***W* questions**
Which typical use cases are presented?Who called? (Age and gender should be documented)Which concerns were stated? (Assessment of the emergency is an overarching goal of the study)When did the concerns occur? (Duration and assessment of the acute situation has to be included in the consideration)Where is the location? (Infrastructure, social environment, etc., should be documented)
**Examples of possible rescue operation cases integrated into the training**
An ambulance is alerted with high priority because of high blood pressure and vertigo. On site, the crew can rule out current life-threatening conditions, only the blood pressure is slightly elevated beyond the patient’s known level after an upsetting argument a few hours before. Anamnesis brings out that the patient is familiar with vertigo and does not have any new kinds of symptoms. So, the ambulance crew cannot find any indication for conveyance at this moment and offers the patient to stay at home unless new kinds of symptoms or decline of general condition occur. The patient prefers to do so, but his daughter presses him to “have a thorough checkup in hospital” and does not concede. The patient is conveyed to the nearest hospital. After the operation, the ambulance crew fills in the questionnaire, describes their working diagnosis as “slightly elevated blood pressure without further symptoms, known vertigo without current worsening” and picks “hospital conveyance” as performed procedure, “consulting the GP in the further course” as appropriate procedure and “patient insists on conveyance by ambulance” (which includes relatives) as reason for hospital conveyance without urgent medical indication.An ambulance is alerted under the heading “attendance operation for fire brigade”. As there is no patient contact during the whole operation and therefore the operation is excluded from this study, the ambulance crew does not fill in the questionnaire.An ambulance and an emergency doctor’s car are alerted with high priority because of acute chest pain. On site, the medical examination shows evidence for an acute myocardial infarction and the patient is quickly treated and conveyed to hospital for further treatment. After terminating the operation, the ambulance crew fills in the web-based questionnaire with the items 1-9 only, because they categorize their treatment as appropriate.An ambulance is alerted with low priority because of a headache on a Saturday. On site, they find a young woman who is healthy except for a cold that has been lasting for “already six days” accompanied by a sinusitis and a feeling of pressure in her head. The symptoms didn’t change during the last days, and she was not satisfied by the advice of her GP and the request to await spontaneous recovery. The ambulance crew repeats the advice of the GP and recommends waiting and see and to contact the GP or alternatively the medical out-of-hours on-call service again if no improvement will occur. The patient insists on an immediate treatment, has never heard of the medical on-call service until now and claims not to be able to drive on her own, so the paramedics call the medical on-call service themselves and ask for a home call. After the operation, they fill in the web-based questionnaire, set their working diagnosis “headache associated with acute sinusitis”, pick “referral to GP or medical on-call service” and “continuance at home” as performed procedure, “consulting the GP in the further course” and “exclusively counseling” as well as “counseling telephonically possible” as appropriate procedures and select “missing transportation opportunities by patient and relatives” and add “patient didn’t know the medical on-call service” for reasons why the patient has not been directed to the appropriate caregiver straightforward.

We explained all phrases used in the questionnaire (Table 1) to precisely define the terms used. Examples for 2 terms are as follows: “social indication” means, for example, a single, immobile older person, a single mother, or a father of an ill child without his own car and without access to public transportation; “medical on-call service” means an on-call service in a suitable medical practice, self-managed by primary care physicians outside regular consultation hours or when a GP is not available.

The questionnaire will be completed once per operation by the ambulance crew, ideally in consultation with both or all 3 crew members and will represent the assessment of the most qualified crew member. The questionnaire can be filled in until the end of the operation.

The following types of operations are excluded: operations involving minor patients (aged <18 years), secondary transports or interhospital transfers, operations cancelled during the approach, operations with no patient found, provisional operations without a patient (eg, fire service operations), and operations in which the patient dies or is found dead on the incident scene. The inclusion and exclusion criteria are listed in Textbox 2.

Inclusion and exclusion criteria for emergency case recording.

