### Design

The key feature of this exploratory, noninterventional, cross-sectional study is a web-based questionnaire (Table 1) for tablets or smartphones. In the first phase, each individual question on the web-based questionnaire was reviewed by an expert panel at the Department of General Medicine at Heidelberg University Hospital, and in the second phase, the questions were discussed with the heads of operations at the rescue coordination centers, as well as with selected paramedics. The focus was on the feasibility of this pilot study. When this study is rolled out (at large scale) there also will be analyses of interrater reliability.

**Table 1 table1:** Questionnaire for ambulance crews on emergency cases.

Item	Content
Operation number	(Free text)
Patient gender	Male Female Gender-diverse
Patient age group (years)	18-24 25-39 40-59 60-64 65-79 ≥80
Operation time on a weekend day or holiday^a^	Yes/no
Operation time during main opening hours of general practitioner care^b^	Yes/no
Classification of operation area (number of inhabitants)	Metropolitan (>100,000) Urban (30,000-100,000) Suburban (10,000-30,000) Rural (<10,000)
Working diagnosis	(Free text)
Treatment or procedure performed (multiple choices possible)	Being conveyed to a hospital Referral to a general practitioner or medical on-call service Continuance at home Patient refused being conveyed Therapeutic measures performed (Free text)
Appropriate treatment or procedure (multiple choices possible; no choice possible)	Being conveyed to a hospital autonomously Calling on the medical on-call service autonomously Consulting the general practitioner for further care Exclusively counseling Counseling by telephone possible Social caretakership Being conveyed by a patient transport ambulance (Free text)
Reasons for being conveyed to a hospital without medical indication (multiple choices possible; no choice possible)	Missed transportation opportunity by patient or relatives Patient insists on being conveyed by ambulance Social indication House call by general practitioner or medical on-call service indicated but not provided Medical on-call service not favored by patient Insecurity of team leader Language barrier (Free text)

^a^As defined by the state in which the operation took place.

^b^Main opening hours were defined as Monday, Tuesday, and Thursday from 7 AM to 7 PM, and Wednesday and Friday from 7 AM to 2 PM.

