The members of the expert panel determined which crucial dimensions of medical emergency treatments will be queried, including (1) working diagnosis, which is the assessment made on site by the ambulance crew with consideration of diagnostics that can be carried out preclinically; (2) procedures, including the ambulance crew’s approach to counseling, treatment, patient transport, and referral to other caregivers; (3) adequacy of care, that is, the assessment of the most suitable form of care, which is carried out by the ambulance crew based on the situation on site; and (4) problems that arise, that is, the evaluation of possible reasons why patients are not directed to the form of care that has been assessed as being most suitable.

The training of the paramedics consists of 5 vital elements. The important questions for assessing their concerns about possible rescue operations (Textbox 1) are described in in-person lectures. The five *W* questions are integrated in the questionnaire and special training is provided.

*W* questions and example cases.

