### Data Analysis

The two main outcomes for our analyses are the number and percentage of inappropriate emergency calls and the reasons for patients being conveyed to a hospital without a medical indication. This total numbers will be further subdivided according to the paramedics’ assessments. Moreover, it is of interest if there are explanatory variables such as patient gender, patient age, operation area, and operation time in the data set that might be associated with inappropriate emergency calls or being conveyed to a hospital without a medical indication. This will be analyzed based on multivariable regression modeling [35]. To calculate frequencies, rates, and percentages, we will use the PROC SQL procedure in SAS (version 9.4, SAS Institute). To perform the multivariable analyses, we will use the PROC GENMOD procedure in SAS. For qualitative analyses, we will use MAXQDA (version 24.1, VERBI Software).

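### The item behind the second main outcome is labelled for conveyed patients, but crews are trained to complete it for patients left at home, and the article states no restriction to conveyed records

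*Protocol article*

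**What the plan says.** Data Analysis names as one of two main outcomes "the reasons for patients being conveyed to a hospital without a medical indication". It also plans multivariable regression of being conveyed without an indication. The tenth item of Table 1 carries almost the same wording: "Reasons for being conveyed to a hospital without medical indication (multiple choices possible; no choice possible").

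The Design section describes the dimension behind this item more widely, as "the evaluation of possible reasons why patients are not directed to the form of care that has been assessed as being most suitable". The Aim section uses both senses: it asks why patients without an indication are brought to an emergency room, and also, more generally, why patients may not get adequate care.

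The example cases used in training also differ. In the first, the patient is conveyed and the item is used "as reason for hospital conveyance without urgent medical indication". In the fourth, the crew is to "pick “referral to GP or medical on-call service” and “continuance at home” as performed procedure", so nobody is conveyed. The crew is nevertheless to "select “missing transportation opportunities by patient and relatives” and add “patient didn’t know the medical on-call service", and this is explained as "for reasons why the patient has not been directed to the appropriate caregiver straightforward".

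**The concern.** A main outcome should be measured in the population it names. Here the outcome and the item label name conveyed patients, while the training material shows crews using the item for anyone who did not reach the suitable caregiver. Because the outcome repeats the item label almost word for word, the natural tabulation is a simple count of item-10 answers. With data recorded as trained, that count would include people who stayed at home.

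Two results are exposed: the number and ranking of reasons for conveyance without indication, and the conveyance regression if a completed item 10 is taken as the event.

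**Working it through.** No figure in the article bears on this point, so there is none to reproduce. The check compares the passages and then shows what mixing would do.

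**1. Who completes item 10?**

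| Source | Patient conveyed? | Item 10 | Meaning |
|---|---|---|---|
| Data Analysis, second main outcome | yes, by definition | – | narrow |
| Table 1, item label | yes, by label | – | narrow |
| Design, fourth dimension | either | – | broad |
| Training case 1 | yes | completed | narrow |
| Training case 2 | no patient contact | no questionnaire | – |
| Training case 3 | yes | skipped | – |
| Training case 4 | no | completed | broad |

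In case 3 the crew "fills in the web-based questionnaire with the items 1-9 only, because they categorize their treatment as appropriate". The item is skipped because care was judged appropriate, and that patient was conveyed. The completion rule shown to crews is therefore appropriateness, not conveyance. Of the two cases that complete item 10, one patient was conveyed and one was not.

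The transport option selected in case 4 is worded slightly differently from Table 1, but Table 1 lists such an option only under item 10, so it is the same item.

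**2. Effect on the count.** Let f be the share of completed items that belong to non-conveyed patients. Of N completed items, N(1−f) belong to the outcome, so an unrestricted count is too large by the factor N / [N(1−f)] = 1/(1−f). The documents give no f. For assumed values:

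- f = 10%: 1/0.90 = 1.11
- f = 30%: 1/0.70 = 1.43
- f = 50%: 1/0.50 = 2.00

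**3. Effect on the distribution of reasons.** The pooled share of a reason is (1−f)·p_conveyed + f·p_not conveyed. Suppose, as an assumption only, that a transport reason applies to 20% of conveyed and 40% of non-conveyed completers:

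- f = 10%: 0.90 × 20% + 0.10 × 40% = 22%
- f = 30%: 0.70 × 20% + 0.30 × 40% = 26%
- f = 50%: 0.50 × 20% + 0.50 × 40% = 30%

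The value for the outcome as defined is 20%. If the two groups share the same distribution of reasons, the percentages and ranking do not move and only the count is wrong.

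**4. Can the groups be separated?** Yes. Item 8 records the procedure performed, with hospital conveyance as one option. Data Collection adds an ambulance feedback code from the control center, although its content is not described. The article does not state that either will be used to restrict the second main outcome.

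**The case against.** The strongest reply is that the article nowhere plans an unrestricted count. The outcome's wording already limits it to conveyed patients, item 8 identifies them, and the filter that builds an analysis set normally belongs in a fuller plan that is not shown. The study is an exploratory pilot, and one example case is thin evidence of how crews behaved. The wider use of the item also serves a question that the Aim section declares.

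Much of this stands. A reader might infer that non-conveyed patients will be counted as conveyed, or that the second main outcome can no longer be answered. The documents support neither: no unrestricted tabulation is written down, and the conveyed subset can be recovered. A reader might also take the non-conveyed share of all low-acuity operations as an upper limit for the contamination. It is not one, because item 10 may be left blank and completion may differ between the groups.

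The contradiction itself remains. It lies between the outcome and item label on one side and the training case and panel dimension on the other, all within this article. It is therefore more than a detail left to an analysis plan. The example is also one of only two that show the item being completed.

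**Conclusion.** The point holds as an inconsistency about which patients the second main outcome covers. It would bias results only if item 10 is tabulated unrestricted or its completion defines the regression event. The count would then be too large by 1/(1−f), with f unknown, and the ranking of reasons would change only if reasons differ by conveyance status. All numerical values above are assumed illustrations. No information has been lost, and the matter can be settled before analysis with variables already collected.

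**What to change.** - Restrict the second main outcome, and the event definition of the conveyance regression, to records with hospital conveyance marked in item 8. Use the records so selected as the denominator for the reasons, and state it.
- Cross-check item 8 against the control-center feedback code, if that code records conveyance. Item 8 allows several choices, so say how a record that marks both conveyance and remaining at home is handled.
- Report item-10 answers from non-conveyed patients in a separate table of barriers to suitable care. This serves the broader question in the Aim section.
- Do not let any choice in item 9 stand alone as the marker of no medical indication. Item 9 includes reaching hospital on one's own or by patient transport ambulance, where the crew may be objecting to the means of transport and not to the hospital visit. Report those choices separately.
- State the comparison set of the regression. Limiting it to operations rated inappropriate is one option, but Data Analysis does not require it.
- Align the item label and the fourth training case for the later large-scale roll-out. This cannot help the present data, whose collection ran to the end of November 2023.

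The cost is some analysis wording, a filter on collected variables, and fewer records in the second main outcome.

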**Inclusion criteria**
Minimum of 1 ambulance involved in the operation (type C according to EN 1789)Crew members were recruited and briefed
**Exclusion criteria**
Provisional operation without patient (eg, fire service operations)Secondary transport/interhospital transferCancellation during approachMinor patients (aged <18 years)Patient dies or is found dead on incident sceneNo patient found

### Setting

The study takes place in the whole area of responsibility of the integrated emergency control center of Ludwigshafen, Germany. This covers an area of about 1200 km^2^ and represents a point of call for over 620,000 inhabitants in 6 administrative districts and independent cities. Its dispatchers answer more than 210,000 calls per year, which result in more than 140,000 EMS operations (average 380 per day) and around 11,000 operations of the fire service annually. The control center has at its disposal 21 ambulances in 12 different locations, as well as 8 emergency doctor’s cars, 1 rescue helicopter, and up to 28 patient transport ambulances (figures obtained via oral communication with the management team of the integrated EMS control center of Ludwigshafen on August 29, 2023). The area of responsibility, with its 6 administrative districts and independent cities, includes the core city of Ludwigshafen as the metropolitan zone, a few cities classified as urban regions, several smaller, suburban towns, and several remote rural townships [34]. The classification of the operation areas used in this survey can be found in Table 2.

**Table 2 table2:** Operation areas of emergency crews.

Operation area	Description
Overall	The area around Ludwigshafen, a city in the federal state of Rhineland-Pfalz, Germany
Metropolitan	The core region of Ludwigshafen
Urban	The cities Speyer, Neustadt, and Frankenthal, as well as the districts Ruchheim and Maudach of Ludwigshafen
Suburban	The cities Bad Dürkheim, Grünstadt, Schifferstadt, Haßloch, Böhl-Iggelheim, Limburgerhof, Mutterstadt, and Bobenheim-Roxheim
Rural	All townships with less than 10,000 inhabitants

### Participant Recruitment

All ambulance crew members under the responsibility of the integrated emergency control center of Ludwigshafen will have access to voluntary participation in this study. [name], a doctoral student, will run several information sessions integrated into conferences at the individual rescue stations. Additionally, a written invitation with information will be sent to every employee via an email distribution list on the internal communications devices of the quality management system. It will include a thorough description of the study content, clarifications concerning the questionnaire, an informed consent form, and a link and QR code supplying access to the web-based questionnaire. Consent will be obtained in the web-based questionnaire; further participation is only possible after providing informed consent.

### Data Collection

During the 10-week period of data collection, access to the web-based questionnaire is available 24 hours a day, 7 days a week. The questionnaire is accessible via the link or QR code and can be filled in using a personal computer, tablet, or smartphone. The questionnaire website has been built exclusively for the study by the department conducting the study. The EMS personnel are encouraged to capture as many operations as possible during this period. The acquisition of the data sets is not bound to a certain time frame after the operations. Although the ambulance crew members must complete the questionnaire only after finishing an operation, the data sets only have to be completed within the period of data collection. The data set of each recorded ambulance operation is directly sent to a dedicated study server within the Department of General Practice and Health Services Research of the University Hospital Heidelberg via secure internet protocols. After closing of primary data collection, additional information and secondary data provided by the control center will be combined with each completely collected data set for interpretation. This comprises the time of day of the alert, the priority of the alert, the keywords of the alert, and a specific feedback code from the ambulance.

The scheduled course of the study is summarized in Figure 1.

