Several limitations of this study should be noted. The whole system of EMS and acute patient care is complex and includes many variables that cannot be examined in this study. For example, the control centers’ process for receiving emergency calls and dispatching ambulances plays a major role during all ambulance operations and the management of acute patients. Assessments of patients’ health condition by dispatchers, EMS personnel, and the patients themselves may greatly differ [43]. Misclassification can occur due to different assessment standards because there are usually no uniform classification criteria. There are approaches to harmonizing the triage and dispatching process, such as an intervention in out-of-hours care call centers in Germany that started in 2017 [44], but currently there exist no mandatory and coherent structures in emergency or rescue coordination centers.

In general, studies concerning the EMS in Germany deal with limited generalizability because of huge regional differences in standard operating procedures for treatment, equipment, staffing of rescue resources, and laws and regulations [45]. This is due to the federal structure in Germany and the accountability for civil protection lying mostly with the federal states or even autonomously with the local authorities [46].

Another limitation is the risk of bias. Operations that the ambulance crew rates as having been inappropriately dispatched are more likely to be captured than operations that fulfill the original functions of the EMS. Additionally, recall bias could occur if the questionnaire is not filled in soon after the end of an operation. Our intention was, in any case, to document all rescue operations regardless of urgency.

Nevertheless, the results of this cross-sectional pilot study may form the basis of further evaluations of possible interventions and pilot projects, the implementation of additional services in urgent care, support for change in the way patients are treated, and political change concerning urgent care in general.

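### The main percentage rests on voluntary records that the protocol expects to favour inappropriate operations, and the plan describes nothing to measure or reduce that bias

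*Protocol article*

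**What the plan says.** Participant Recruitment states that all crew members of the control center's area "will have access to voluntary participation in this study". Under Data Collection, "The EMS personnel are encouraged to capture as many operations as possible during this period", and "The acquisition of the data sets is not bound to a certain time frame after the operations", provided the entry is made within the collection period. Neither section requires consecutive or sampled recording.

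Data Analysis names as one of two main outcomes "the number and percentage of inappropriate emergency calls". The Abstract makes the percentage of unnecessary missions the overarching goal.

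The Discussion gives the direction of selection: "Operations that the ambulance crew rates as having been inappropriately dispatched are more likely to be captured than operations that fulfill the original functions". It adds that the intention was nonetheless to document every operation.

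On the routine data, Data Collection says that after closing "additional information and secondary data provided by the control center will be combined with each completely collected data set for interpretation". It lists the fields: "This comprises the time of day of the alert, the priority of the alert, the keywords of the alert, and a specific feedback code". Data Management repeats that the secondary data will be linked and described. Neither section mentions records of operations for which no questionnaire was submitted. Data Analysis describes frequencies, percentages and multivariable regression.

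**The concern.** The denominator of the main percentage is the set of operations that crews chose to record. If the choice depends on the crew's own rating of the operation, selection acts on the outcome itself. The percentage is then shifted, and more records narrow the interval around the shifted value without moving it back.

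The routine data are the natural means of seeing how recorded operations differ from the rest. As described, they are joined to completed questionnaires, so the comparison is not part of the plan. The Discussion hopes that the results will inform new services and political change. A headline figure with an acknowledged but unmeasured upward bias is a weak basis for that.

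**Working it through.** **Inputs from the protocol**
- Volume: calls "which result in more than 140,000 EMS operations (average 380 per day") (Setting).
- Collection period: 10 weeks, or 70 days (Data Collection).
- Expected proportion: 30% to 35%, mid-point 32.5% (Discussion).
- Expected yield: several thousand operations (Results), with no exact figure.

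**Assumptions, not in the protocol**
- Capture ratio r, the chance that an inappropriate operation is recorded divided by the chance that an appropriate one is: 1.25 to 3.
- Yield n: 2,000 to 9,000.

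**1. The protocol's own figure.** 140,000 / 365 = 383.6 per day, which agrees with the stated average of 380.

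**2. Volume in the window.** 380 × 70 = 26,600 EMS operations of all kinds. The eligible number is smaller and not given, so this is not a usable denominator for a capture share.

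**3. Effect of selective capture.** With true proportion p, observed proportion = p·r / (p·r + 1 − p).

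| Assumed r | p = 30% | p = 32.5% | p = 35% |
|---|---|---|---|
| 1.5 | 39.1% | 41.9% | 44.7% |
| 2 | 46.2% | 49.1% | 51.9% |
| 3 | 56.2% | 59.1% | 61.8% |

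For example, p = 0.325 and r = 2 give 0.65 / (0.65 + 0.675) = 0.491. Even r = 1.25 turns 30% to 35% into 34.9% to 40.2%.

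**4. False agreement with expectation.** A true 20% with r = 2 gives 0.40 / (0.40 + 0.80) = 33.3%. A true 25% with r = 1.5 gives 0.375 / (0.375 + 0.75) = 33.3%. Either would look like confirmation of the 30% to 35% that the Discussion expects.

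**5. Comparison with sampling error.** The 95% half-width is 1.96·√(p(1 − p)/n). For p of 30% to 35% it is about 2.1 points at most for n = 2,000 and about 1.0 point for n = 9,000. At r = 1.5 and p = 32.5% the shift is 41.9 − 32.5 = 9.4 points.

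**6. What remains possible without data on unrecorded operations.** Worst-case bounds with capture share c are c·obs to c·obs + (1 − c). With an assumed c = 20% and 35% observed, they are 7% and 87%: valid, but too wide to be useful.

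**7. What a full extract could achieve.** Assume that half of operations are low priority with 50% inappropriate and half are high priority with 15%, so the true value is 32.5%.
- If capture depends on priority alone (ratio 2), the raw figure is (2 × 0.5 × 0.50 + 0.5 × 0.15) / (2 × 0.5 + 0.5) = 38.3%. Reweighting to all operations returns 32.5%.
- If capture depends on the crew's rating (r = 2), the raw figure is 49.1%. The within-stratum figures are 66.7% and 26.1%, so reweighting gives 0.5 × 66.7% + 0.5 × 26.1% = 46.4%.

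The second case is the mechanism that the Discussion describes. Weighting helps, but only in part.

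**The case against.** The protocol discloses this bias, calls the study an exploratory pilot, and states that all operations were meant to be documented. Capture-rate reporting, weighting and sensitivity analyses are also often left to a full protocol or analysis plan, and neither is shown here. These points bear on tone and severity. They do not remove the point: disclosure neither measures nor reduces the bias, and the remedy depends on which data are requested, which the article itself describes. A later analysis plan cannot compare recorded with unrecorded operations if the latter were never requested. For a pilot meant to precede a large-scale roll-out, the capture rate is also a basic feasibility result.

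A reader might infer more than the text supports, in three ways.
- *Linkage is restricted to submitted questionnaires.* Data Collection does not use a word such as only, and Data Management states no restriction. The operation number is collected (Table 1), so nothing described prevents a wider extract. That the control center holds the listed fields for every operation is plausible but not stated.
- *Nothing can be done about the bias.* A table over assumed capture ratios needs only the observed percentage, and bounds can be formed for an assumed capture share. Both are possible under the present plan; they are just not described.
- *The study will capture a small, known share of operations.* Dividing several thousand by 26,600 would mislead. Setting lists patient transport ambulances, emergency doctor's cars and a helicopter besides the 21 ambulances. Textbox 2 also excludes minors, secondary transports, cancellations and other operations. The share among eligible operations is higher by an unknown amount.

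**Conclusion.** The point holds as a design weakness with an inexpensive improvement. Following the plan as described gives a main percentage that the protocol's own reasoning expects to be too high, with nothing described to measure or reduce the excess. The direction comes from the protocol; the size is unknown. The shift from 32.5% to between 41.9% and 59.1% rests entirely on assumed ratios of 1.5 to 3 and shows sensitivity, not a prediction. Under those ratios selection would far outweigh sampling error at any plausible yield. The capture share cannot be derived from the document.

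The conclusion also rests on reading the linkage sentence in its plain sense, without sight of the full protocol.

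**What to change.** In Data Collection, extend the extract already planned for after closing to all ambulance operations in the collection window. Use the fields already listed (time, priority, keywords, feedback code) and apply the exclusions as far as those fields allow. Age under 18, for instance, may not be identifiable from them. Then report:

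1. the capture rate, overall and by stratum of the listed fields, with the number of questionnaires whose free-text operation number could not be matched;
2. a comparison of recorded with unrecorded operations on those fields;
3. the raw percentage with a weighted percentage beside it, the latter labelled a partial correction because capture may depend on the crew's own rating;
4. a sensitivity table over assumed residual capture ratios, for example 1 to 3.

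State the main percentage as applying to recorded operations unless these analyses support a wider claim.

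The cost is a larger extract, some analysis work and a wider interval for the weighted figure. Ethical Considerations requires ethics-committee approval of protocol modifications and release of the new protocol to participants, so that step must be allowed for. Station or ambulance identifiers would improve the weighting, but should be added only if compatible with the anonymity promised to participants in the same section.
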